### Participants

All consecutive eligible adult patients (age >18 years) with a diabetic foot lesion corresponding to Wagner 2 to 4 that has continuously existed for a minimum of four weeks, who meet all inclusion criteria and no exclusion criteria, may be included in the trial. Chronic diabetic foot wounds after adequate wound pretreatment (debridement and/or wound cleansing) as well as amputation wounds resulting from a planned amputation underneath the upper ankle joint (lat.: Articulatio talocruralis) may be considered for inclusion. Therefore the main part of the wound is not allowed to be located above the upper ankle joint. Before randomization, inclusion in the trial and any trial-related procedure the participant must have provided written informed consent. Figure 3 provides a full overview of the inclusion and exclusion criteria. Reasons for non-enrolment or non-eligibility will be documented for all patients who fulfil the inclusion criteria but who are not included in the trial.

**Figure 3 Fig3:**
[figure not shown]
**Inclusion and exclusion criteria of the DiaFu study.** The table shows the required diagnosis and the inclusion and exclusion criteria for DiaFu participants.

Any inability of the patient to respond to requests, to adequately assess risk or to comply with the requirements of the course of study, both in the inpatient and outpatient therapy episode, must be considered as non-compliance. If, in the estimation of the clinical investigator, a patient is non-compliant at the time of inclusion or is expected to be non-compliant during the course of the trial, this patient may not be included. Contraindications for the application of a NPWT device that result from a recommendation or a warning from the Food and Drug Administration (FDA) or from the manufacturers’ guidelines for product use are exclusion criteria for this trial. Patients with presence of necrotic tissue with slough and scab that cannot be debrided are not allowed to be included in the trial. Prior to randomization and start of study treatment, if necessary, a sufficient debridement or a radical removal of necrotic tissue in terms of an amputation should be carried out. If parts of the necrotic tissue cannot be removed by debridement or amputation, the patient should not be included in the study. Special attention has to be paid to exposed blood vessels within the wound or the direct wound surrounding that cannot be protected or that carry an increased risk of bleeding with relevant circulatory effects. If a sufficient covering is not possible, the patient should not be included in the study Patients may not be included if they are receiving anticoagulation therapy or are suffering from a higher grade impaired clotting function and have a heightened risk for bleeding with relevant circulatory effects if those patients are in outpatient care during the time of inclusion. If treatment systems which are based on the principle of NPWT have been used at the study-related foot lesion within a period of at least six weeks prior to the start of the study these patients may not be included in the trial. This is due to the objective of the study to demonstrate and evaluate a clear therapeutic effect of each treatment arm.

### Intervention and control

In the intervention group medical devices using the principle of NPWT will be applied on the study wound [7, 8]. This therapeutic technique uses a vacuum dressing to promote healing. The therapy involves the controlled application of sub-atmospheric pressure to the local wound environment, using a sealed wound dressing connected to a vacuum pump. NPWT promotes wound healing through optimization of blood flow, decreasing local tissue edema and removing excessive fluid from the wound bed. These physiologic changes facilitate the removal of bacteria from the wound. Additionally, the cyclical application of sub-atmospheric pressure alters the cytoskeleton of the cells in the wound bed through microstrain, triggering a cascade of intracellular signals that increase the rate of cell division and subsequent formation of granulation tissue. Moreover, this system has been shown to also cause macrostrain, bringing the edges of the wound closer and also stimulating wound bed granulation. NPWT as interim therapy should be discontinued once the condition of a wound is suitable for closing, either spontaneously or surgically.

Table 1 gives an overview of the NPWT devices used within the trial. Medical devices used within the trial are all CE certified products. All NPWT devices and dressings to be utilized in this study bear the CE mark and will be operated within normal conditions of use and according to clinical and manufacturers guidelines. Dressing changes are recommended to be performed according to manufacturer’s instructions with frequency adjusted by the clinician as appropriate. Contraindications and precautions will be noted.

**Table 1 Tab1:** **Used medical products within the trial**

KCI	Smith & nephew
**NPWT devices**	
V.A.C. Freedom^®^	Renasys^TM^ GO
Acti V.A.C.^®^	Renasys^TM^ EZ Plus
INFO V.A.C.^®^	
V.A.C. Ulta^®^	
**Dressing**	
V.A.C^.®^ Granufoam^®^ (black)	Foam dressing (RENASYS^TM^ –F/P)
V.A.C^.®^ Granufoam^®^ silver^®^	Gauze dressing (RENASYS^TM^ –G)
V.A.C.^®^ Whitefoam^®^	

The table shows the NPWT devices of Kinetic Concepts Incorporated (KCI) and Smith & nephew used within the trial.

Control therapy is defined as any conventional moist wound therapy according to local clinical standards and guidelines [6]. Healthcare providers are obligated to provide patients with best practice and standard of care. In the control arm it is permitted to apply every local wound treatment standard used in the respective study site that does not have an experimental status or is based on the principle of NPWT.

To ensure the quality of local wound treatment during the course of the study, the study sites are trained for both the intervention arm and the control arm. The manufacturers are responsible for the training with the NPWT systems and consumables (dressing materials). The German Society for Wound Healing and Wound Treatment (German: Deutsche Gesellschaft für Wundheilung und Wundbehandlung e.V.) provides parts of their curriculum and performs the training for the control arm.

### Primary and secondary endpoints

Time until complete (100% epithelization) wound closure and the number of wound closures in each treatment group achieved in the maximum study treatment time of 16 weeks (112 days) are the primary endpoints of the DiaFu study. Complete wound closure is defined by 100% epithelialization of the wound (no granulation tissue visible), no drainage, no sewing material and no need for wound dressing or adjuvants. The assessment of complete wound closure is primarily based on the central blinded review of photographs performed by independent analyzers. Complete wound closure can be achieved either by surgery or by secondary intention. However, surgical intervention (for example wound suture, skin grafting or flap transplantation) is allowed only if the wound bed is prepared adequately. Sustainment of complete wound closure has to be proven by a satisfactory follow-up examination of the area 14 days after the intervention (wound closure verification visit). If the wound cannot be closed before the end of the maximum treatment time of 16 weeks, a study visit to assess the wound status and for evaluation of the secondary endpoints is performed.

Secondary clinical endpoints are the time until complete wound closure within the study time of six months, the number of wound closures per treatment group achieved within six months, the time until optimal preparation of the wound bed for further treatment (a minimum of 95% granulation), recurrences, amputations with incidence and extent, the wound size over time (area of wound opening, maximal length and width (cm^2^)) and the composition of wound tissue (percentage of epithelial layer, granulation tissue and fibrin).

The incidence of serious adverse events (SAEs) including mortality of any cause within six months from the time of initiation of therapy, incidence of device-related adverse events (ADEs) and incidence of wound-related adverse events (AEs) occurring within the study treatment time of 16 weeks or until wound closure confirmation are considered to be safety endpoints of this trial.

Furthermore, patient reported outcomes (PRO) will be evaluated. Quality of life (QoL) is measured using the questionnaire EQ5D. The questionnaire will be completed by the participant at inclusion, end of the maximum treatment time or end of the therapy and at the six-month follow-up visit . Furthermore, during study visits participants will be asked to provide their assessments of pain with a numerical rating scale (0 to 10). Participants will be asked to provide an estimate of their wound-associated pain of the last 24 hours at each trial visit.

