
### Aim of the DiaFu study

This RCT is designed to prove that NPWT therapy leads more frequent and earlier to complete healing of diabetic foot wounds as compared to conventional moist wound therapy. Furthermore, it aims to show that NPWT therapy is also safe and effective when provided in an ambulatory care setting and to prove its overall cost-effectiveness. This trial is designed to comply with all quality requirements (randomized trial, low potential for bias; see Discussion section) of IQWiG and G-BA, as well as other European authorities.

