### Statistical analysis

The analysis of the primary and secondary endpoints will be performed according to the intention-to-treat principle (ITT). There will be no interim analysis. The ITT analysis population will include all randomized participants who have a valid baseline and at least one valid post baseline wound assessment (examination). For the ITT analysis population, participants will be assigned to the treatment group based on the randomization schedule, regardless of the treatment actually received. As a secondary approach a per protocol (PP) analysis will be performed excluding patients with any serious protocol deviations and changes of wound treatment. The rates of wound closure will be compared using Fisher’s exact test and time to complete closure will be compared using the Log-rank test. Safety data will be presented on an ‘as treated’ basis where patients will be grouped according to the exact wound treatment performed. Safety and secondary endpoints will be analyzed using conventional univariate testing. For the analysis of the primary efficacy endpoint missing values will be incorporated as censored values.

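### The window for wound- and device-related AEs and the date of the second EQ-5D can depend on wound healing, so the arms may be compared over slightly different times

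*Protocol article*

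**What the plan says.** All of the following is in the protocol article.

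- **AE window.** Under *Primary and secondary endpoints*, the incidence of device-related and wound-related AEs is a safety endpoint for events "occurring within the study treatment time of 16 weeks or until wound closure confirmation". Confirmation requires a verification visit 14 days after closure.
- **Serious events.** The same sentence gives SAEs a window that does not depend on healing, covering "mortality of any cause within six months from the time of initiation of therapy".
- **EQ-5D.** The form is completed "at inclusion, end of the maximum treatment time or end of the therapy and at the six-month follow-up visit". The first and third occasions are fixed; the second is not.
- **Analysis.** *Statistical analysis* states: "Safety and secondary endpoints will be analyzed using conventional univariate testing". Safety patients are grouped by treatment received. No allowance for length of observation is mentioned.
- **Expected healing.** *Aim of the DiaFu study* says the trial is "designed to prove that NPWT therapy leads more frequent and earlier to complete healing of diabetic foot wounds". *Power calculation* assumes 45% closure on NPWT and 30% on control within 16 weeks.

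**The concern.** Closure is the primary outcome. If AE recording stops when closure is confirmed, the outcome under test sets each patient's time at risk. The arm that heals faster then has less time in which to record an event, and a comparison of crude incidences leans towards it. The trial expects that arm to be NPWT, and showing that NPWT is safe in ambulatory care is one of its stated aims.

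The second EQ-5D raises a similar problem. If it is completed when therapy ends, healed patients answer earlier after randomisation than unhealed ones. *Health economic evaluation and analysis* uses patient-reported outcomes as an effectiveness measure, so the timing matters beyond the clinical report. The phrase for the end of therapy is also undefined. *Intervention and control* describes NPWT as an interim therapy that stops once the wound is suitable for closing, so in that arm the date could precede closure.

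**Working it through.** **The plan's own figure.** With 45% against 30%, two-sided 5% and 80% power, the pooled formula gives

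n = [1.96·√(2·0.375·0.625) + 0.8416·√(0.45·0.55 + 0.30·0.70)]² / 0.15² = 162.3 per group.

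The arcsine formula gives 161.9. The stated 162 is reproduced and not disputed; it is used here only for the closure rates and the group size.

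**Inputs from the article:** closure by day 112 of 0.45 (NPWT) and 0.30 (control); 14 days from closure to confirmation; maximum of 112 days.

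**Assumptions, because the article gives no figures:** the pattern of closure times; the AE risk; an AE hazard that is equal in both arms and unchanged after closure; a window that ends at the earlier of day 112 and confirmation.

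**Step 1: AE observation time, constant closure hazard.**

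- h = −ln(1 − p)/112, which is 0.005338 per day (NPWT) and 0.003185 per day (control).
- Mean of min(closure + 14, 112) = 14 + [1 − exp(−98h)]/h.
- NPWT: 14 + 0.4073/0.005338 = 90.3 days. Control: 14 + 0.2681/0.003185 = 98.2 days.
- Ratio 90.3/98.2 = 0.92, that is 7.9 days or 8% less on NPWT.

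**Step 2: other closure patterns, same 45% and 30%.**

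| Assumed closure times | NPWT (days) | Control (days) | Ratio |
|---|---|---|---|
| Constant hazard | 90.3 | 98.2 | 0.92 |
| Uniform, days 28–112, both arms | 98.9 | 103.3 | 0.96 |
| NPWT days 28–84, control days 56–112 | 93.1 | 107.3 | 0.87 |
| All closures days 84–112 | 110.4 | 111.0 | 0.995 |

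**Step 3: effect on crude AE incidence.** Take a true 16-week risk of 20% in both arms, so a = −ln(0.80)/112 = 0.001992 per day. With constant-hazard closure,

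incidence = 1 − exp(−14a)·{[h/(h + a)]·[1 − exp(−98(h + a))] + exp(−98(h + a))}.

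- NPWT: 1 − 0.9725·(0.3732 + 0.4876) = 16.3%.
- Control: 1 − 0.9725·(0.2448 + 0.6021) = 17.6%.
- Risk ratio 0.92. The difference of 1.35 percentage points is 162 × 0.0135 = 2.2 patients per arm.

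Over the four patterns and true risks of 10–30%, the risk ratio runs from 0.87 to 1.00. A nominal 5% two-sided test with 162 per arm rejects between 5.0% and 10.8% of the time, and 6.2% in the case worked above.

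**Step 4: the other reading of the window.** If it ends at the later of the two limits, nobody is observed for less than 112 days. Only closures after day 98 add time, at most 14 days and about 7 on average. These are 0.5927 − 0.55 = 4.3% of NPWT patients and 0.7319 − 0.70 = 3.2% of controls, so means rise by about 0.3 and 0.2 days. The imbalance is then negligible.

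**Step 5: second EQ-5D.** If it is completed at closure or at day 112, its mean date under constant hazard is p/h: 0.45/0.005338 = day 84.3 on NPWT and 0.30/0.003185 = day 94.2 on control. Over the four patterns the gap is 2 to 17 days. About 45% and 30% of forms would precede day 112. If the form waits for verification, 1 − exp(−98h) gives about 41% and 27%.

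**The case against.** The case for leaving this alone has several parts.

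- **The clause does not say which limit governs.** A wound may close as late as day 112 and still need 14 days of confirmation, so the second limit may be there to extend the window for late closers. This stands: the calculation is conditional on the earlier-of reading. The clause could also attach to wound-related AEs only.
- **Fewer events after healing may be a true benefit.** Closure means full epithelialisation with no drainage and no dressing. If AE risk is near zero after confirmation, a fixed 112-day count gives nearly the same result as the stated window. This also stands, and it limits the size of the problem. A fixed window would still show that benefit directly instead of presuming it.
- **Constant hazard from day 0 may exaggerate.** The Discussion says chronic wounds are slow to start healing, and the earlier NPWT trial cited there reported an average of 96 days to closure on NPWT. Later closures give ratios of 0.96 to 0.995.
- **The analysis plan can deal with it.** It can choose rates per patient-time or a time-to-event method; the wording on univariate tests does not strictly exclude a log-rank test. It cannot recover events that fell outside the recording window, or a week-16 EQ-5D that was never taken.

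A reader might also infer that re-opening or serious infection after confirmation goes uncounted. The article does not support that: recurrences and amputations are secondary endpoints without this cut-off, and SAEs run to six months. What may be lost is non-serious wound- or device-related AEs after confirmation.

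**Conclusion.** The point holds as a cheap improvement. As written, the AE window and the second EQ-5D date can both depend on an outcome that the trial expects to differ by arm. On the earlier-of reading, NPWT patients would be observed for about 8% less time (0–13% by closure pattern), and crude AE incidence would modestly favour NPWT to the extent that risk persists after confirmed closure. The direction follows from the trial's own planning rates; the size rests on assumed closure patterns and AE risks.

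Three stronger readings are tempting but unsupported:

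- That AE observation averages 84 against 94 days, a gap of about 11%. Those figures stop at closure, whereas the AE window runs to confirmation.
- That the second EQ-5D is taken at closure. The article ties it to the end of therapy, which it does not define, so the dates in step 5 are illustrative.
- That EQ-5D will be compared without regard to baseline. The article is silent on this, univariate tests can use change scores, and such detail commonly belongs to the analysis plan.

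The primary endpoints, sample size, SAEs, mortality, recurrences, amputations and six-month EQ-5D are not affected.

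**What to change.** 1. Count wound- and device-related AEs over a common 112 days from randomisation in every patient, whether or not closure has been confirmed. Report rates per patient-time as a supplement.
2. Make the six-month EQ-5D, adjusted for baseline EQ-5D, the main comparison of patient-reported outcomes. Either treat the second EQ-5D as descriptive or fix it at week 16 for everyone.

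The cost is slightly longer recording of non-serious AEs in patients whose wounds close early and, if the second EQ-5D is fixed at week 16, a change in the date of one short questionnaire for them. These patients are already followed to six months. The rest is a change of wording in the endpoint definition and the analysis section.

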### Health economic evaluation and analysis

In addition to the evaluation of clinical treatment effectiveness, a prospective assessment of health economic issues with a focus on the direct medical costs of wound treatment will be performed. This includes assessment of the parameters relevant for inpatient and outpatient resource use. A cost-effectiveness analysis using PRO and the number of wound closures as effectiveness measures will be performed. The economic evaluation is performed from the perspective of the German social insurance over the time horizon of the study period. To estimate costs the resource use is measured in natural units (for example duration of dressing changes in minutes). The average resource use per patient is calculated and priced with opportunity cost approximated over German market prices or schedule prices (for example wage agreements for staff costs). A sensitivity-analysis is performed by replacing the mean costs and effects with the upper and lower bound of the respective 95% confidence interval. Costs and effectiveness results are synthesized in an incremental cost-effectiveness ratio.

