## Abstract

**Background:**

In August 2010, the Federal Joint Committee (G-BA) decided that negative pressure wound therapy (NPWT) would not be reimbursable in German ambulatory care. This decision was based on reports from the Institute for Quality and Efficiency in Health Care (IQWiG), which concluded that there is no convincing evidence in favor of NPWT. The aim of this diabetic foot study (DiaFu study) is to evaluate whether the clinical, safety and economic results of NPWT are superior to the results of standard wound treatment.

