## Discussion

### Trial preparation and organization

Within a European tender the study was initiated by the statutory health insurance in Germany. A consortium of 19 statutory health insurance funds including the Federal Association of Local Health Insurance Funds (AOK-Bundesverband), the Association of Substitute Health Funds (vdek-Verband der Ersatzkassen e.V.), and the Sickness Fund for Miners and Seamen (Knappschaft) including the Maritime Health Insurance Fund (See-Krankenkasse). These statutory health funds are the central contact for the study project and all associated health insurance funds provide integrated care contracts for ambulant NPWT of study patients. The Institute for Research in Operative Medicine (German: Institut für Forschung in der Operativen Medizin (IFOM) of the University of Witten/Herdecke is an independent scientific institute that is responsible for the scientific conception, analysis and reporting of the study. Furthermore, IFOM monitors the compliance with regulatory and quality requirements. The University of Witten/Herdecke has taken over the sponsorship of the trial. A management company, Gesundheitsforen Leipzig (GFL), is responsible for the logistics, the financial aspects and the study site selection, as well as patient recruitment for the study. The study database is provided and hosted by the GFL. The trial is funded by the participating statutory health insurance companies and the manufacturers Kinetic Concepts Incorporated (KCI) and Smith & Nephew (S&N). Both companies provide the NPWT systems in the assigned regions of Germany as well as all necessary information about the used medical devices and associated consumable supplies. Recruitment of study patients is performed in hospitals and outpatient facilities with a specific qualification for the treatment of chronic diabetic foot wounds all over Germany. A webpage provides more information about the overall study project. The website can be found using the uniform resource locator http://www.wound-care.de.

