### Ensuring outpatient care of study participants with NPWT

In Germany outpatient care with NPWT is not generally reimbursed. To ensure the optimal patient-centered care and to avoid any bias, the participating health insurance companies are providing integrated care contracts for NPWT in the ambulant treatment sector. Moreover, integrated care contracts are provided for the ambulant NPWT of up to 7000 patients with acute and chronic wounds in Germany.

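### The described sensitivity analysis varies sampling error only, so the uncertain price of ambulatory NPWT goes untested in the cost-effectiveness ratio

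*Protocol article*

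**What the plan says.** All of this is in the protocol article.

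- **Health economic evaluation and analysis** sets the viewpoint: "The economic evaluation is performed from the perspective of the German social insurance over the time horizon of the study period". Resource use is measured in natural units, averaged per patient and "priced with opportunity cost approximated over German market prices or schedule prices"; staff wages are the only priced example. Uncertainty is handled as follows: "A sensitivity-analysis is performed by replacing the mean costs and effects with the upper and lower bound of the respective 95% confidence interval". The results are combined in an incremental cost-effectiveness ratio, with wound closures as one of the effect measures.
- **Abstract, Background** reports the 2010 decision that "negative pressure wound therapy (NPWT) would not be reimbursable in German ambulatory care". **Ensuring outpatient care of study participants with NPWT** repeats that "In Germany outpatient care with NPWT is not generally reimbursed" and adds that "the participating health insurance companies are providing integrated care contracts for NPWT in the ambulant treatment sector". It also gives the scale: "integrated care contracts are provided for the ambulant NPWT of up to 7000 patients with acute and chronic wounds in Germany".
- **Trial preparation and organization** names two manufacturers as co-funders and says: "Both companies provide the NPWT systems in the assigned regions of Germany". Table 1 lists six NPWT devices and five dressings across the two companies.
- **Aim of the DiaFu study** includes proving overall cost-effectiveness. The abstract's Discussion ties the results to a pending reimbursement decision.

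**The concern.** A confidence interval for a mean cost answers the question of how far the mean could move had other patients been sampled. It does not ask what the ratio would be if an NPWT day or dressing set cost the insurer something else. For most resources that matters little, because a payer knows its tariffs. NPWT outside hospital is different: it is not generally reimbursed, it is covered in the study by special contracts, and it comes from two suppliers with separate territories. The price that would apply after a positive decision need not equal a contract price or a list price used during the trial.

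NPWT use also differs between the arms by design, since control treatment may not rest on the NPWT principle. Its price therefore enters the incremental cost directly. A decision-maker reading one ratio with sampling bounds could not tell whether the conclusion would survive another price, nor at what price NPWT would stop adding cost.

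**Working it through.** **1. The plan's own figure.** The economic section states no price, cost, ratio or threshold. The only computed design figure is in Power calculation: 162 per group for closure rates of 45% and 30%, alpha 0.05, power 80%. Using the two-sided pooled-variance formula:

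n = [1.960 × √(2 × 0.375 × 0.625) + 0.842 × √(0.45 × 0.55 + 0.30 × 0.70)]² / 0.15² = (1.342 + 0.569)² / 0.0225 ≈ 162.3

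This rounds up to 163 against 162 stated, and power at 162 is 79.9%. The figure is reproduced to within rounding. It supplies the two inputs used below: a closure difference of 0.15 and 162 patients per arm.

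**2. What the confidence bounds contain.** Mean cost per patient in an arm is the sum over resources of (unit price × mean use). If unit prices are constants, the only random part is use per patient. The 95% half-width as a share of the arm mean is 1.96 × CV / √162, where CV is the coefficient of variation of cost per patient (assumed, as the article gives none):

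| Assumed CV | Half-width |
|---|---|
| 0.5 | 7.7% |
| 1.0 | 15.4% |
| 1.5 | 23.1% |

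This width shrinks as patients are added, whereas uncertainty about a price does not. If patients were costed at their own supplier's price, the spread between suppliers would enter the variance, but the interval would still be centred on one price mix.

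**3. How the ratio depends on price.** Let D be the difference between arms in mean NPWT days per patient, p the price per NPWT day (device and consumables), K the difference in all other costs, and E the difference in closure rate. Then

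ratio = (D × p + K) / E

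This is linear in p with slope D / E, whatever K is. The cost-neutral price is p* = −K / D, which is positive only if NPWT saves other resources.

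**4. Size at the planned difference.** Shift for 10 euro per day = 10 × D / 0.15. The step and the days are assumptions.

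| Mean NPWT days (assumed) | Shift, euro per extra closure |
|---|---|
| 20 | 1,333 |
| 30 | 2,000 |
| 40 | 2,667 |
| 60 | 4,000 |

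**5. Price against sampling error in the effect.** Take an illustration with 28 NPWT days and K = 0, both assumed.

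- Vary price, effect fixed at 0.15: 25, 50 or 100 euro per day gives 28 × p / 0.15 = 4,667, 9,333 or 18,667 euro per closure, a fourfold range.
- Vary effect, price fixed at 50 euro (incremental cost 28 × 50 = 1,400): the standard error is √[(0.2475 + 0.21) / 162] = 0.0531, so the 95% interval for the difference is 0.045842 to 0.254158. The ratio runs from 1,400 / 0.254158 = 5,508 to 1,400 / 0.045842 = 30,540, about 5.5-fold.

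The described analysis covers the second source and leaves the first at a fixed value.

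**The case against.** The economic evaluation is one paragraph of a condensed article. A list of unit prices, their sources and further one-way analyses may sit in a fuller document, and the article does not say that no other sensitivity analysis will be run. Failing to name the NPWT price source is therefore missing detail and not an error. That stands, and this point does not rest on it. It rests on the method that is described, which cannot test price as it is worded. A price list elsewhere would settle the base case without making confidence bounds vary price.

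It is also fair to say that step 5 shows sampling error in the effect moving the ratio at least as much as a fourfold price range. That stands too, and it rules out any claim that price is the dominant uncertainty.

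A reader might infer more than the text supports:

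- *That no ambulatory price exists.* The article says NPWT is not generally reimbursed and then describes integrated care contracts, which could supply a payer-side price that the costing rule already permits.
- *That NPWT is costed once, at a single device price.* The article gives a general rule for all resources and states no NPWT price. Several devices and two suppliers are involved.
- *That the economic conclusion hangs on the device price.* No price, NPWT duration, cost or threshold is given, and inpatient, outpatient and staff resources also enter.
- *That the ratio moves one-for-one with price.* It moves linearly, by 133 to 400 euro per 1 euro at 20 to 60 days. It is proportional to price only if K is zero.

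Finally, the stated lack of reimbursement concerns ambulatory care, while therapy may start in hospital. The payer-price question therefore bears on ambulatory NPWT days, and applying a price change to all NPWT days can overstate the shift.

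**Conclusion.** The point holds in a limited form. The sensitivity analysis as described reflects sampling variation and leaves unit prices unvaried, although the payer's price for ambulatory NPWT is uncertain on the article's own account and the study is meant to inform a reimbursement decision. At a closure difference of 0.15, each 10 euro per day is worth about 1,333 to 4,000 euro per extra closure for 20 to 60 NPWT days. A smaller closure difference would make the slope steeper. Whether that is large against the ratio itself cannot be judged, because no baseline cost is documented.

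This is a useful addition to a stated method. It affects no clinical endpoint, test or sample size.

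**What to change.** In Health economic evaluation and analysis, keep the confidence-bound analysis and add a deterministic one-way analysis. It should recompute the incremental cost-effectiveness ratio over a stated range of NPWT device and consumable prices, including the integrated-care contract price and each manufacturer's price, and report the price at which NPWT becomes cost-neutral. Showing ambulatory and inpatient NPWT days separately would confine the price range to the sector where the payer's price is open.

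The cost is one or two sentences and a short table or graph, with no new patients. It does require NPWT days and consumables to be among the recorded natural units. The article does not list them explicitly, so this should be confirmed. The downside is a little more analysis and an economic conclusion that is conditional on price.
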